## Background and rationale

Social contacts play a critical role in the transmission dynamics of infectious diseases. Understanding who people are interacting with, how frequently they are doing so, and under what circumstances these interactions occur is essential for predicting the spread of diseases such as COVID-19 and developing targeted interventions to mitigate their impact.

The COVID-19 pandemic significantly altered patterns of social interaction in the UK and elsewhere as evidenced by the CoMix survey conducted during the pandemic. Some of these changes are likely to have persisted after the acute phase of the pandemic due to cultural shifts such as remote working. To better understand current social contact patterns in the UK and their potential implications for infectious disease transmission, we will conduct a comprehensive social contact survey in 2024. As in previous surveys, we will collect detailed demographic information on participants and how they make contacts (quantity, duration, closeness, frequency, etc.). We will also investigate key unknowns not assessed previously in the UK, such as how contacts vary seasonally, the assortativity of contacts by socioeconomic status and ethnicity, and contact with animals, factors which may have substantial implications for transmission and health outcomes.

This research will contribute valuable insights into social contact patterns in the UK and their relationship to infectious disease transmission. By collecting up-to-date data on social contacts and their associated characteristics, this study will support ongoing efforts to protect population health and minimise the burden of infectious diseases.

## Aims and Objectives

This study aims to collect detailed data on social contacts in the UK, including key demographic information, to:

- Describe current patterns of social interaction and assess how they have changed compared to previous surveys
- Investigate the extent to which social contacts vary according to factors such as age, gender, socioeconomic status, and ethnicity
- Examine how social contact patterns change seasonally (e.g., winter vs. summer, school terms vs. holidays)
- Identify any notable trends or patterns that could inform the development of future public health interventions
- Create stratified contact matrices to parameterise mathematical models.

# Study Design

We will conduct several cross-sectional surveys in the United Kingdom in summer and in winter, covering holiday/non-holiday periods in each (term time/school holidays and pre-Christmas/ Christmas). We will survey both adults and children about their mixing behaviour to fully capture differences in different age groups.

## Enrollment Procedure

We aim to survey at least 10,000 individuals in total, split evenly between the summer and winter surveys. We will use a market research company to ensure a sample representative of the national population in terms of age, gender, geographical location, socioeconomic status, and ethnicity via quota sampling. Children enrolled in the survey will be encouraged to complete the survey themselves, and the questions will be asked in such a way as to be understandable to all.

Participants will be invited to the study via email, which will explain the purpose of the study and how they will take part. If they accept, participants will be first asked to record demographic information about themselves (“participant information”). Following this, they will then be instructed to record their contacts made on the following day (the “survey day”) in a prospective diary-based approach using a mobile-accessible app or webpage. On the survey day, participants will be encouraged to make a note of contacts (e.g. their initials) as they happen, or in regular time intervals (e.g. at lunchtime, dinnertime, before bed), to maximise recall. At the end of the survey day, individuals will be asked to then record the detailed demographic information and contact event information for the contacts made on the day (“contact information”).

Participants will be invited until the specified quotas have been filled. Effort should be made to ensure equal spread across the different days of the week to capture work/school week and weekend effects. Participants will be offered a small financial incentive to take part (e.g. Amazon vouchers or similar).

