## Statistics and Data Analysis

### Sample Size

We define an appropriate minimum sample size for this study as whether a difference in overall mean contacts can be detected compared to previous surveys conducted in GB / the UK - POLYMOD (Mossong et al., fieldwork 2005-6) and CoMix (Jarvis et al., final survey Nov-Dec 2022). There were substantial differences in the overall mean daily contacts reported in each of these two surveys (11.74 and 6.5, respectively) with contributing factors being the lasting impacts of the COVID-19 pandemic and rise of widespread digital communication and social media. Thus, we predict that overall contact rates will have decreased compared to POLYMOD, and increased compared to the final CoMix survey. As such, we specify a meaningful change as being at least a 10% decrease in contacts versus POLYMOD and at least a 10% increase versus the final CoMix survey. Another difference is that of the degree of overdispersion in daily contact rates; POLYMOD reported a theta of 2.78, though a secondary analysis of CoMix indicated much greater overdispersion (0.58; lower values indicating greater overdispersion).

With a sample size of at least 463 we will be able to detect a 10% decrease with 80% power compared to the POLYMOD contact survey conducted in 2005-6 (Table 1), assuming overdispersion parameter of 2.78; a sample size of at least 3517 is required to detect a difference compared to the final CoMix survey in 2022, assuming an overdispersion parameter of 0.58.

The final sample size will be subject to budget, though we will target 5000 in each seasonal round to reduce the risk of sparsity in the contact matrices. Quotas on age, sex, ethnicity, and geographic location will be used to ensure that a representative sample of the UK population is reached and exceeded for minority ethnic groups (target: to double the representation of non-white participants in the survey).

**Table: Minimum sample sizes required to detect changes in overall contacts compared to previous surveys, given assumptions on magnitude of change and overdispersion.**

| Previous survey                    | Number of participants | Overall mean contacts | Relative change in number of reported contacts compared to previous survey | Dispersion parameter | Sample size required to achieve power |

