## Changes to protocol

| Original protocol                                                                                                                                                                                                                       | Changes in final protocol                                                                                                                                                                                                                                                                                                                                             |
|-----------------------------------------------------------------------------------------------------------------------------------------------------------------------------------------------------------------------------------------|-----------------------------------------------------------------------------------------------------------------------------------------------------------------------------------------------------------------------------------------------------------------------------------------------------------------------------------------------------------------------|
| Study design
“We will conduct several cross-sectional surveys in the United Kingdom in summer and in winter, covering holiday/non-holiday periods in each (term time/school holidays and pre-Christmas/ Christmas).”          | Study design
Due to issues with the quality of the data collected during the late summer period in 2024, additional surveys were conducted over the autumn and winter period. As such, we were unable to make formal comparisons between these time periods; however, we report differences in contacts between school term-time and holidays by age group. |
| Sample size
The final sample size will be subject to budget, though we will target 5000 in each seasonal round to reduce the risk of sparsity in the contact matrices. Quotas on age, sex, ethnicity, and geographic location | Sample size
We conducted a cross-sectional social contact survey in the UK United Kingdom from 13th December 2024 to 10th February 2025. Participants were recruited from a UK-based internet panel, using quota                                                                                                                                            |

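### Nothing requires quotas or weekday balance to hold within holiday and term periods, and age group is the only stratifier named for the term-time versus holiday contrast, so other compositional differences may confound it

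*Protocol*

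**What the plan says.** The Protocol's Aims and Objectives include "Examine how social contact patterns change seasonally (e.g., winter vs. summer, school terms vs. holidays"), so the term/holiday comparison serves a stated aim.

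On recruitment, Enrollment Procedure says "Participants will be invited until the specified quotas have been filled". The only balance over time that it asks for within a survey is by weekday: "Effort should be made to ensure equal spread across the different days of the week". The design was first set out as several surveys "covering holiday/non-holiday periods in each (term time/school holidays and pre-Christmas/ Christmas"), with the sample "split evenly between the summer and winter surveys". Sample Size adds that "we will target 5000 in each seasonal round" and that "Quotas on age, sex, ethnicity, and geographic location will be used".

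The final-protocol column of Changes to protocol describes one main fieldwork window, 13 December 2024 to 10 February 2025. Its quotas are on gender, country, region, household income and education, with a deliberate oversample of non-White participants and of children. It targets a total of 10,000 over the whole study. A later boost round, 22 February to 10 March 2025, was aimed at children and people aged 70 and over. The same column says that formal comparisons between time periods could not be made, but "we report differences in contacts between school term-time and holidays by age group".

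Statistical Analysis plans negative binomial regression stratified by participant demographics in general. It does not mention school period.

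**The concern.** Under a rule that invites people until quotas fill, a cell that closes early contributes no later respondents. If cells fill at different speeds, the mix of respondents changes with calendar date. In this study the calendar date also decides whether a diary falls in holiday or term, so drift in composition and the exposure of interest can move together.

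Reporting by age group removes the age part of any drift. It leaves gender, ethnicity, region, income, education and weekday mix within an age group. The Protocol itself expects contacts to vary by gender, socioeconomic status and ethnicity (Aims and Objectives) and between the working week and the weekend (Enrollment Procedure). An imbalance in any of these would appear in the age-specific differences and could be taken for an effect of school holidays.

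**Working it through.** **1. What is fixed, side by side.** The Protocol gives no figure for this contrast. Its computed sample sizes (463 and 3517) concern overall means against POLYMOD and CoMix and do not bear on it. The first check is therefore of the text.

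- Length of the main window: 19 days in December + 31 in January + 10 in February = 60 days. It contains the Christmas holiday and term time. The Protocol gives no term dates and no number of respondents in each period.
- Boost round: 7 days in February + 10 in March = 17 days, aimed at selected age groups.
- Quota or target by holiday/term period: none stated in either column of the changes table.
- Weekday spread by period: none stated. An equal spread overall does not imply an equal spread in each period.
- Control tied to the contrast: age group only.
- Level at which quotas were filled (whole window, survey or shorter block): not stated.

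A quota set per round would not remove the problem, because the main window is presented as a single round containing both kinds of period. Only quotas met within each period would do so, and none are stated.

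**2. How large a shift could be.** All shares and contact differences below are assumptions; the Protocol gives none.

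*Demographic mix.* Suppose a subgroup has contacts lower by a fraction d than everyone else, and is a share pH of holiday and pT of term respondents in an age group. With no true period effect, the apparent term/holiday ratio is

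R = (1 − d·pT) / (1 − d·pH).

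Taking pH = 0.25 and pT = 0.45:

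- d = 0.10: 0.955/0.975 = 0.979, a shift of −2.1%
- d = 0.20: 0.910/0.950 = 0.958, a shift of −4.2%
- d = 0.30: 0.865/0.925 = 0.935, a shift of −6.5%

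*Weekday mix.* Suppose weekend contacts are 20% lower, with a weekend share of 2/7 in one period and w in the other. Then R = (1 − 0.2w) / (1 − 0.2 × 2/7), where the denominator is 0.943.

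- w = 0.40: 0.920/0.943 = 0.976, a shift of −2.4%
- w = 0.50: 0.900/0.943 = 0.955, a shift of −4.5%

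*A second parametrisation.* Let 40% of one period belong to a subgroup with r times the contacts of the rest, and let that share be δ higher in the other period: R = [1 + (0.4 + δ)(r − 1)] / [1 + 0.4(r − 1)].

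- δ = 0.05, r = 1.2: 1.09/1.08 = 1.01
- δ = 0.10, r = 1.5: 1.25/1.20 = 1.04
- δ = 0.20, r = 2: 1.60/1.40 = 1.14

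The last case needs both a doubling of contacts and a 20-point difference in share. Signs follow from the assumptions and could go either way, so two sources of imbalance may add or partly cancel.

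**The case against.** The strongest counter-argument is that the mechanism is inferred. The invitation rule was written for a design of several surveys with a target per seasonal round, and nothing says at what level quotas were applied in the final one. No accrual by date is given. The only groups reported as recruiting more slowly than expected are children and people aged 70 and over. Both are age groups, and age is the variable already stratified. The weekday instruction asks for an equal spread, and a large weekend imbalance in one period assumes that it failed there. The general analysis section already plans demographic stratification, and the covariates for a secondary contrast commonly sit in a statistical analysis plan, which is not shown. Finally, the changes table gives up formal period comparisons, so this one is descriptive.

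Most of this stands, and it rules out three stronger readings:

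- *Quotas were filled once over the whole window, so the two periods differ by construction.* A reader might infer this from the invitation rule and the overall target of 10,000. The documents do not state it; they only fail to exclude it.
- *The bias approaches the 10% that the Protocol calls meaningful.* That is reached only by multiplying the two worst assumed cases in the same direction (0.935 × 0.955 = 0.893, or −10.7%). The 10% is also defined for overall means against POLYMOD and CoMix, not for this contrast.
- *The two periods play the part of confirmatory comparison groups.* No test, estimate or power is attached to them.

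What remains is that the recruitment text is a protocol matter and contains no safeguard by period, and that the one control tied to the contrast is age. General demographic stratification does not balance the two periods unless period is in the same model. A descriptive difference will still be read as an effect of holidays.

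**Conclusion.** The point holds as a risk of confounding that the Protocol leaves open. Quotas and weekday balance are not required within holiday and term periods, and age group is the only stratifier named for the contrast. The two periods can therefore differ within an age group on gender, ethnicity, region, income, education and weekday.

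The size of any resulting shift cannot be computed from the document. On assumed values, one source of imbalance at a time gives about 2% to 6% in most cases worked; the second parametrisation runs from 1% to 14% between its mildest and most extreme settings. These figures show that the risk is plausible; they do not estimate a bias. The conclusion assumes that quota cells filled at different speeds, which is documented only for age groups, and that no adjustment is specified in an analysis plan that is not at hand.

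**What to change.** Estimate the term/holiday ratio within each age group from the negative binomial model already planned, with gender, ethnicity, region/country, household income, education and day of the week as covariates. Alternatively, standardise both periods to the same demographic mix and to a 5:2 weekday:weekend split. In either case, tabulate participant composition and weekday mix by period, so that readers can see how far the two samples differ.

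The demographic variables are listed under Measurements. Survey date is not listed there, but Enrollment Procedure ties each diary to a defined survey day, so day of the week should be recoverable; this needs confirming.

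The cost is a change of analysis wording and slightly wider intervals in sparse age groups. Where an age group is too small for the full covariate set, standardising on fewer variables is a reasonable fallback. Fieldwork is complete, so setting quotas by period is not part of the fix.

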## Measurements

Participants will be asked to record the following information about themselves:

- Age
- Gender
- Geographical location (first part of postcode)
- Ethnicity
- Household income
- Occupation
- Highest level of education
- Housing status (homeowner, private renter, etc.)
- Household size
- 5Q-5D health-related quality of life
- High-risk status (offered flu vaccine)
- Current symptoms

- Vaccine confidence
- Public transport
- Distance travelled in past week

Participants will be asked to record the following information about their contacts:

- Time of contact
- Age
- Gender
- Geographical location (first part of postcode)
- Ethnicity
- Occupation
- Contact location (home/work/school/etc.)
  - Indoor/outdoor
- Duration of contact
- Physical/non-physical contact
- Is the contact a household member (yes/no)
- Frequency of contact (how many days out of the week do you typically interact with this person?)
- Attendance of large contact events
  - Option to record high numbers of contacts which would be difficult to record individually
- Contact with animals (pets, livestock (chickens, pigs, cattle, etc.))

## Statistics and Data Analysis

### Sample Size

We define an appropriate minimum sample size for this study as whether a difference in overall mean contacts can be detected compared to previous surveys conducted in GB / the UK - POLYMOD (Mossong et al., fieldwork 2005-6) and CoMix (Jarvis et al., final survey Nov-Dec 2022). There were substantial differences in the overall mean daily contacts reported in each of these two surveys (11.74 and 6.5, respectively) with contributing factors being the lasting impacts of the COVID-19 pandemic and rise of widespread digital communication and social media. Thus, we predict that overall contact rates will have decreased compared to POLYMOD, and increased compared to the final CoMix survey. As such, we specify a meaningful change as being at least a 10% decrease in contacts versus POLYMOD and at least a 10% increase versus the final CoMix survey. Another difference is that of the degree of overdispersion in daily contact rates; POLYMOD reported a theta of 2.78, though a secondary analysis of CoMix indicated much greater overdispersion (0.58; lower values indicating greater overdispersion).

With a sample size of at least 463 we will be able to detect a 10% decrease with 80% power compared to the POLYMOD contact survey conducted in 2005-6 (Table 1), assuming overdispersion parameter of 2.78; a sample size of at least 3517 is required to detect a difference compared to the final CoMix survey in 2022, assuming an overdispersion parameter of 0.58.

The final sample size will be subject to budget, though we will target 5000 in each seasonal round to reduce the risk of sparsity in the contact matrices. Quotas on age, sex, ethnicity, and geographic location will be used to ensure that a representative sample of the UK population is reached and exceeded for minority ethnic groups (target: to double the representation of non-white participants in the survey).

**Table: Minimum sample sizes required to detect changes in overall contacts compared to previous surveys, given assumptions on magnitude of change and overdispersion.**

| Previous survey                    | Number of participants | Overall mean contacts | Relative change in number of reported contacts compared to previous survey | Dispersion parameter | Sample size required to achieve power |
|------------------------------------|------------------------|-----------------------|----------------------------------------------------------------------------|----------------------|---------------------------------------|
| POLYMOD (2005-6)                   | 1012                   | 11.74                 | -10%                                                                       | 0.36                 | 463                                   |
| CoMix (final survey, Nov-Dec 2022) | 2991                   | 6.5                   | +10%                                                                       | 1.72                 | 3517                                  |

[figure not shown]

**Figure: Required sample size to achieve power exceeding 0.8 and 0.9 for the comparisons of a change of -10% (or -20%) mean contacts versus POLYMOD and +10% (or +20%) mean contacts versus the final CoMix survey.**

## Statistical Analysis

Count models (negative binomial regression) will be employed to estimate the mean number of daily contacts and account for the likely substantial heterogeneity between individuals. These will be stratified by the different demographic characteristics of the participants to account and assess for any differences between groups. We will also develop social contact matrices considering assortativity of contact between different age groups, as well as investigate the additional dimensions of ethnicity, socioeconomic status, and other relevant factors. These estimates will inform ongoing and future response efforts to guide public policy decisions.

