| 
will be used to ensure that a representative sample of the UK population is reached and exceeded for minority ethnic groups (target: to double the representation of non-white participants in the survey).
                                                                                                                                                                                                                                                                                                                                                                                                                                                                                                                                                                                                                                                                                                                                      | 
sampling to ensure a close representation of the UK population in terms of gender, country, region (as defined by the Office for National Statistics (ONS), within England), household income, and education. We aimed to recruit at least 10,000 adult and 1,000 child participants, deliberately oversampling non-White participants and children in order to reduce data scarcity when conducting stratified analyses. A total sample size of 10,000 individuals was targeted over the duration of the study. As recruitment rates for children and individuals aged 70+ were lower than expected, we conducted a second “boost” round of the survey from 22nd February to 10th March 2025 to increase representation in these age groups.
 |

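### Age-group means and age contact matrices pool diaries from different calendar periods, because only children and people aged 70+ had a later boost round, and the analysis names no adjustment for diary period

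*Protocol*

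**What the plan says.** The Aims and Objectives include comparing contacts by age, gender, socioeconomic status and ethnicity, describing term and holiday patterns, and producing stratified matrices for use in models.

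Under Enrollment Procedure, recruitment is open-ended: "Participants will be invited until the specified quotas have been filled". The one request for balance over time concerns the day of the week: "Effort should be made to ensure equal spread across the different days of the week to capture work/school week and weekend effects".

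The final-protocol column of Changes to protocol (Sample size) gives the fieldwork dates. The main round ran "from 13th December 2024 to 10th February 2025". Then, "As recruitment rates for children and individuals aged 70+ were lower than expected", a boost round was held "from 22nd February to 10th March 2025 to increase representation in these age groups". The quotas there are set "in terms of gender, country, region (as defined by the Office for National Statistics (ONS), within England), household income, and education", with oversampling of non-White participants and children. Calendar date is not among the quota variables.

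Statistical Analysis plans negative binomial models and says of them: "These will be stratified by the different demographic characteristics of the participants to account and assess for any differences between groups". It also plans age matrices, with ethnicity and socioeconomic status as further dimensions. The changes table has rows for study design, sample size and measurements, but none for the analysis. Its study design row says that formal comparisons between time periods were not possible and that term-time and holiday contacts will be reported by age group.

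**The concern.** The protocol itself treats time of year as a driver of contacts: it lists term against holiday as an objective and was designed around pre-Christmas and Christmas periods. The boost then gave two age groups a block of diaries from a period in which other ages were not targeted. Pooling both rounds gives each age group its own holiday share, and stratifying by participant characteristics does not remove that difference.

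Age is the main dimension of the matrices. Part of a difference between children and working-age adults could therefore reflect when the diaries were completed. A matrix row for children would describe a different calendar from a row for adults. A larger sample would not reduce this bias.

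**Working it through.** The protocol states no figure on this point, so there is none to reproduce. The check uses its dates and assumed values for the rest.

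**From the documents**
- Main round, 13 December to 10 February: 19 + 31 + 10 = 60 days.
- Boost, 22 February to 10 March: 7 + 10 = 17 days, all after the main round.

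**Assumed, because the documents do not give them**
- School holiday 21 December to 5 January: 11 + 5 = 16 days. With diaries spread evenly over the main round, the holiday share is w = 16/60 = 0.267.
- No school holiday in the boost period. Any holiday days there would shrink the effect.
- Ratio of holiday to term contacts for children: r = 0.5 to 0.7.
- Share of child diaries supplied by the boost: s = 0.25 to 0.50.

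**Formula**
The expected mean is the term mean times 1 − h(1 − r), where h is the holiday share of diaries. Without the boost h = w; with it h = q = w(1 − s). The shift in the pooled mean relative to the main-round calendar is

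[1 − q(1 − r)] / [1 − w(1 − r)] − 1.

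**Results for w = 0.267**

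| r | s | q | Ratio | Shift |
|---|---|---|---|---|
| 0.7 | 0.25 | 0.200 | 0.940/0.920 | +2.2% |
| 0.7 | 0.50 | 0.133 | 0.960/0.920 | +4.3% |
| 0.5 | 0.25 | 0.200 | 0.900/0.867 | +3.8% |
| 0.5 | 0.50 | 0.133 | 0.933/0.867 | +7.7% |

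**Sensitivity**
- A milder ratio of 0.9 with a boost share of 10% gives +0.3%.
- If 40% of main-round diaries fell in the holiday, the mildest case (r = 0.7, s = 0.25) gives 0.91/0.88 = +3.4% and the strongest (r = 0.5, s = 0.50) gives 0.90/0.80 = +12.5%.
- For people aged 70+ the ratio could lie on either side of 1. At r = 1 there is no shift, and above 1 its sign reverses. No figure is offered for them.

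**Ethnicity and socioeconomic status**
The documents give no fill dates or recruitment speeds for these groups. With equal holiday shares the spurious ratio between two groups with no true difference is 1.00. Shares of 17% and 27% would give 1.01 to 1.06 as r goes from 0.9 to 0.5. Nothing in the protocol says which case applies.

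**The case against.** The strongest reply is that the Statistical Analysis section is a short summary, and that covariates and weighting usually belong in an analysis plan, which was not available for this review. Silence about diary date does not exclude it. That stands against saying that the estimates are confounded; the supportable statement is that they are open to confounding unless adjusted. It does not dispose of the point. The section does state what the models are stratified by, and the boost changed the calendar mix by age without a matching change to the analysis.

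Second, the promised report of term and holiday contacts by age group lets a reader compare ages within a period. This is a partial answer. It shows that diaries can be classified by period, but it does not standardise the pooled means or the matrix rows.

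Third, the main round ran to 10 February for all groups, so every group could supply diaries after Christmas. That is true and limits the size. On the assumptions above, main-round diaries are 73% term and pooled child diaries 80 to 87% term, a gap of 7 to 13 percentage points.

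A reader might also infer three stronger things that the documents do not support:
- That ethnic and socioeconomic contrasts are already distorted, because easy-to-recruit groups finished before or during Christmas. No fill dates are given.
- That making the matrix reciprocal mixes two periods. The section does not mention reciprocity.
- That the shift should be judged against the 10% change in the Sample Size section. That threshold is set for the overall mean against earlier surveys, not for differences between groups.

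**Conclusion.** The point holds for age. Children and people aged 70+ alone were targeted by a round held wholly after the main round, the only time balance requested is by day of the week, and the planned stratification uses participant characteristics only. Provided main-round recruitment was spread similarly over time across ages, the boosted groups have the smaller holiday share, and their means, contrasts and matrix rows are open to confounding by diary period.

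For children the shift is about 2 to 8% under the central assumptions, and smaller or larger under others. It rests wholly on assumed holiday dates, contact ratio and boost share, so it is an illustration and not an estimate. For ethnicity and socioeconomic status, imbalance is possible because quotas fill without calendar balance, but it is not demonstrated, and a table of diary dates would settle it. This is a worthwhile and inexpensive improvement, not a flaw that invalidates the survey.

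**What to change.** Amend Statistical Analysis as follows.

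- Add diary period (school holiday or term, by the date of the diary) and weekday/weekend to the negative binomial models, with an age-group-by-period interaction where numbers allow.
- Report age-group means, and weight matrix rows, to one stated calendar mix common to all groups.
- If reciprocity is imposed on the matrices, apply it after this weighting.
- Tabulate the holiday share of diaries by age, ethnicity and socioeconomic group.
- Give separate term and holiday matrices only where cell counts allow. Taking the target of 1,000 children as the total, a boost share of 25 to 50% and a 27% holiday share leave about 750 × 0.267 = 200 down to 500 × 0.267 = 133 child holiday diaries, before any split by age band or ethnicity. The protocol already names sparsity as a concern.

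No new data are needed, since the promised term and holiday report already requires diaries to be classified by period. The cost is precision, mostly for children and people aged 70+ in the holiday period. As a guide, weighting a boosted group back to a 27% holiday share multiplies the variance by about w²/q + (1 − w)²/(1 − q), if the variance is similar in both periods. This is 0.356 + 0.672 = 1.03 for a 25% boost share and 0.533 + 0.621 = 1.15 for 50%. Intervals would be about 1 to 7% wider (square roots 1.01 and 1.07). A different calendar mix would change this cost.
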